### Eligibility criteria

All the students of class 8 of the selected schools in the urban area of Mangalore will be eligible to participate in the study.

### Study participants

Students studying in 8
^th^ standard (middle school) in the selected schools in the urban area of Mangalore. The study population will be restricted to the students of 8
^th^ standard since the students will be available in the selected schools for the entire duration of the study and loss to follow up is nil or minimal. Since the study has one year duration of follow up, students from 10
^th^ standard will not be selected since they will complete their studies and shift to a different college.

### Exclusion criteria

Students whose parents do not give consent for their ward to participate in the study, students who do not assent to participate in the study and students who are not present on the day of baseline evaluation will be excluded from the study.

### Randomization technique

The list of schools situated in Mangalore will be obtained from the Block Education Officer/Deputy Director of Public Instruction. A comprehensive list of all eligible schools i.e., schools with classes 8 and above will be prepared. All the schools located within the limits of Mangalore City Corporation will be considered clusters. The study will employ cluster randomization, with clusters being allocated in a 1:1 ratio to the intervention arm and control arm. Randomization of schools will be done to accommodate 10 schools each in the intervention and control arm by simple randomization technique.

### Sampling technique

The study participants will be selected from the 8
^th^ standard of selected schools. In schools with multiple sections of the same class, a simple random sampling technique will be employed to select one section, assuming a batch size of 40 students in each section. If the batch selected after simple random sampling has less than 40 students, the next batch will be selected by simple random sampling without replacement method, to reach the desired sample of 40 from the clusters.

The selected schools in the intervention arm would receive the comprehensive multicomponent modular intervention and the control group would not receive any intervention from the investigator. The students in the control group will undergo routine physical health education as per the school curriculum. They will be offered the comprehensive modular intervention only after the end of the final data collection.

### Multi-component modular intervention

The intervention designed will be a combination of a health education session, distribution of information flyers, and an activity designed to promote self-motivated behaviour change.

Based on suggestions from subject experts, a thorough literature assessment, and interaction with local stakeholders, a health education module will be created. This will be a multi-component educational module in English containing pertinent textual and illustrated/pictorial information curated according to the local context. The module has four main components:
•
**Component 1: Sedentary behaviour**
This will provide information as to what constitutes sedentary behaviour and the various activities which are considered sedentary in various settings including school and at home.•
**Component 2: Screen-based and non screen based sedentary behaviour**
This will introduce the participants to the concept of screen time, and screen based and non screen based sedentary time. The behaviours constituting them will be explained using pictures and real life examples.•
**Component 3: Effects of sedentary behaviour**
This component will explain to the participants the harmful effects of excessive screen time and how screen time is associated with reduced physical activity and sedentary behaviour, unhealthy eating and poor quality sleep. The section will also introduce the participants to the health effects of sedentary behaviour on the body and mind.•
**Component 4: Reducing screen time and sedentary behaviour**
This component will introduce participants to various methods designed to reduce screen time like setting screen time limits for a day, turning off notification sounds in their phones to avoid picking up their phone more often, practising screen-free time e.g. avoiding screen use during lunch breaks, avoiding using screens before going to sleep, encouraging a screen-free bedroom, avoiding the use of eBooks to read novels, and taking part in screen-free physical activities that they enjoy to promote a healthy lifestyle. Since classroom learning can account for the least active time of a child’s day, incorporating physically active learning in between classes can help in reducing the amount of time children spend sitting down each day. The component will introduce the students to the concept of ‘movement breaks’ where the students will be taught how to break continuous periods of sedentary behaviour during the school hours. They will be taught small activities that they can do while still inside the classroom that we call ‘chairobics’. They will also be taught about how movement helps to increase blood flow around the body and to the brain so that they can feel alert, concentrate better and are ready to learn and think during the class.

The selected schools in the intervention arm would receive the multi-component modular intervention. Along with the educational module, a flyer depicting the effects of excessive screen time, risks of sedentary behaviour and tips for reducing screen time will be distributed to all the students in the selected class. Each student will also be given a notebook to log the duration of screen time during school and non-school hours (screen time tracking) duration of physical activity and duration of sleep until the end of the intervention period. At the end of every week’s recording, students will be encouraged to write a reflection on challenges or difficulties they faced in following a healthy lifestyle and how to overcome them.

### Intervention procedure

The class size of the selected schools is expected to be 40. The educational intervention will be delivered by the primary investigator. Three sessions at two monthly intervals will be conducted in the schools (Baseline, 2
^nd^ month and 4
^th^ month) selected to receive the modular educational intervention. The duration of each session will be 40 minutes.

The students in the schools selected for the control arm will not receive any intervention from the investigators. They will continue receiving the physical activity routine as per the school curriculum. The school will be offered the modular intervention only at the end of the final data collection.

### Operational definitions

**Screen time:** This refers to how much time a person spends using screen-equipped electronic devices, such as computers, televisions, game consoles, cell phones, and tablets, irrespective of whether the activity is carried out when physically active or sedentary.
^
28
^

**Screen-based sedentary time:** This refers to the duration an individual spends engaged in sedentary activities while using electronic devices with screens in any context (e.g., school, work, recreation). Sedentary activities involve minimal physical movement or energy expenditure and typically involve sitting or lying down for extended periods.
^
28
^

**Recreational screen time:** This refers to the period during which an individual engages in screen-based activities for leisure, entertainment, or personal enjoyment. This includes the time spent using screen-equipped electronic devices, such as computers, televisions, game consoles, cell phones, tablets, and other similar devices, for activities that are not work or education-related.
^
28
^

**Non-screen-based sedentary time:** This refers to the amount of time spent engaging in sedentary activities that don’t use screens.
^
28
^

### Instruments used for data collection

A pre-tested, content-validated semi-structured questionnaire will be used for data collection. The questionnaire was prepared after an extensive review of the literature and consultation with subject experts, and will include the following sections:

**Section 1:** Socio-demographic details

**Section 2:** HELENA (Healthy Lifestyle in European Adolescents) Screen-Time-Based Sedentary Behaviour Questionnaire
^
29
^

**Section 3:** Non-Screen-Based Sedentary Behaviour Questionnaire

**Section 4:** Physical Activity Questionnaire for Adolescents (PAQ-A)
^
30
^

**Section 5:** Anthropometric measurements based on STEPS questionnaire
^
31
^

### Healthy Lifestyle in European Adolescents Screen-Time-Based Sedentary Behaviour Questionnaire (HELENA)
^
29
^

HELENA questionnaire will be used to assess the screen-associated sedentary behaviour among the adolescents. The questionnaire requires adolescents to report how much time they typically spend on a variety of sedentary activities on weekdays and weekends.

The sedentary activities captured by the questionnaire include:
(i)Watching television(ii)Playing games on the computer(iii)Playing games on a console(iv)Academic web browsing(v)Nonacademic web browsing (E.g., Watching videos on YouTube)(vi)Browsing through social media (such as Facebook, Instagram, etc.)

Depending on the time spent on these activities, the participants will choose one from the following options: (i) 0 hours (ii) < 1/2 hr (iii) ½ -1 hr (iv) 1-2 hrs (v) 2-3 hrs (vi) 3-4 hrs (vii) >4 hrs. Weekly time will be calculated by taking the mean time in the selected category and applying the formula: [(weekdays x 5) + (weekend x 2)] /7. A final screen-based sedentary score will be generated by adding the time reported for each category.
^
29
^

### Non-Screen Based Sedentary Behaviour Questionnaire

This section of the questionnaire was prepared after an extensive review of the literature. It captures the duration of time spent by adolescents during school days and holidays, carrying out sedentary activities which do not involve the use of screens. The activities included are as follows:
(i)Educational purposes: (number of hours sitting in the class, hours spent studying, doing homework, tuition class outside of school)(ii)Recreational purposes: (hours spent sitting and playing games such as chess, carrom board, playing a musical instrument, hours spent on hobbies while sitting down such as reading novels, painting, arts and crafts etc)(iii)Travel purposes: (hours spent in car, bus, school van etc.) and social purposes (talking with friends and family).

Depending on the time spent on these activities, the participants will choose one from the following options: (i) 0 hours (ii) < 1/2 hr (iii) ½ -1 hr (iv) 1-2 hrs (v) 2-3 hrs (vi) 3-4 hrs (vii) >4 hrs. Weekly time will be calculated by taking the meantime in the selected category and applying the formula: [(weekdays x 5) + (weekend x 2)] /7. The time reported for each category will be added up to produce a final non-screen-based sedentary time.

### Physical Activity Using the Physical Activity Questionnaire for Adolescents (PAQ-A)
^
30
^

It is an 8-item self-report questionnaire developed to assess the adolescents’ levels of physical activity over the previous 7 days. Each of the eight (PAQ-A) questionnaire items is scored between 1 and 5, and the mean score across all items is the total PAQ score. A score of 1 indicates low physical activity, whereas a score of 5 indicates high physical activity.

### World Health Organization (WHO) Stepwise Approach to Surveillance (STEPS)
^
31
^

This is a structured process for gathering, examining, and sharing information on noncommunicable diseases (NCDs) and their risk factors. Anthropometry measurements will be taken as per the standard and protocol outlined in WHO-STEPs.

### Data collection

The Institutional Ethics Committee (IEC) of Kasturba Medical College, Mangalore, has accepted the protocol (IECKMCMLR-02/2023/57). The trial has been registered with the Clinical Trial Registry-India (CTRI) (REF/2023/04/066280). Before the commencement of the study, the Block Education Officer, Mangalore will be approached to obtain the list of schools in Mangalore and to get the necessary permission to conduct the study in schools.

Permission to conduct the study in the selected schools will be obtained from the school administration. The school administration/Principal will be told the objectives of the study. On receiving the formal approval, the schools will be visited on a previously informed date. The study will be carried out among the students studying in class 8 of the selected schools. In case there are multiple sections for the same class, one of the sections will be selected for the study using simple random sampling.

Since the participants in the study are under the age of 18 years, documented parental consent will be required before their enrollment in the study. The information sheet and consent form will be distributed to the students of the selected class on the first visit to be shared with their parents. On the second visit, a written assent will be taken from the students whose parents have consented and the questionnaire will be distributed.

### Baseline data collection

A self-administered questionnaire will be used to gather the demographic data, which includes information like age, gender, class, section, address, contact information, and the parents’ or guardians’ occupations. The study participants will be asked about their screen- and non-screen-based sedentary time as well as their physical activity. Anthropometric measurements like height, weight, waist and hip circumference will be collected using standardized techniques.
^
31
^

Following the collection of baseline data, the schools selected for intervention will receive the multi-component modular intervention. Three sessions at two monthly intervals will be conducted in these schools. (Baseline, second month and fourth month) Both groups will complete the questionnaires at baseline, and two, four and six months of follow-up. Anthropometric measurements will be taken at baseline and sixth month of follow-up) Outcome will be assessed at each point of time in both intervention and control arm students. Confidentiality and anonymity will be maintained throughout the study (
Figure 1).

**Figure 1. f1:**
[figure not shown]
Study CONSORT diagram.

### Procedure for anthropometric measurements

**Measurement of weight**

A digital weighing scale will be used to measure weight. The patient will be requested to take off their shoes, socks, and any additional footwear they may be wearing before being instructed to place one foot on either side of the scale. The participant will be instructed to stand still, with their arms at their sides and their face front. The scale will record the weight in kilos to the nearest 0.1 cm. After each use, the scale will be reset to zero.
^
31
^

**Measurement of height**

A portable stadiometer will be used to measure the height. The participant will be directed to take off their shoes, slippers, and sandals in addition to their hat, cap, hair bows, comb, and ribbons. The participant will be instructed to face the investigator and stand on the board. He/She will be instructed to stand with their feet together, knees upright, and heels touching the backboard. He or she is instructed to maintain a straight-ahead gaze and to keep their eyes level with their ears. By lowering the measuring arm to the patient’s head, the reading will be measured to the nearest 0.1 cm.
^
31
^

**Body mass index**
^
32
^

Body Mass Index (BMI) will be calculated using the
equation (2):

$$\mathrm{BMI}=\frac{\text{Weight}\;\left(\text{in}\;\mathrm{kg}\right)}{\text{Height}\;{\left(\text{in meter}\right)}^{2}}$$
(2)

The presence of being overweight and obesity will be assessed by computing BMI for age z scores and comparing them to the age- and sex-specific BMI z score +1 cut-offs published by the World Health Organization.
^
30
^ The interpretation of BMI z scores is as follows: The presence of being overweight and obesity will be assessed by computing BMI for age z scores and comparing them to the age- and sex-specific BMI z score +1 cut-offs published by the World Health Organization.
^
30
^ The interpretation of BMI z scores is as follows:

Overweight: >+1 SD (equivalent to BMI 25 kg/m
^2^ at 19 years)

Obesity: >+2 SD (Equivalent to BMI 30 kg/m
^2^ at 19 years)

**Measurement of waist circumference**

Waist circumference will be taken halfway between the bottom of the last rib and the top of the iliac crest (hip bone), at the end of breathing, with arms at the sides using a measuring tape. The subject is instructed to put the tape over themselves. It will be instructed for the subject to stand with their feet together, their weight evenly spread over both feet, and their arms relaxed by their sides. Only one measurement will be made to the closest 0.1 cm.
^
31
^

**Measurement of hip circumference**

Hip circumference will be calculated using a measuring tape. The participant must stand with their feet together, their weight evenly distributed over both feet, and their arms at their sides. The tape would be applied to the buttocks’ largest circumference. Measurements will be made to the nearest 0.1 cm at the level of the tape.
^
31
^

### Outcome variables

1.Mean screen sedentary time (SST) and non-screen sedentary time (NSST)2.Level of physical activity3.Association of BMI, waist circumference hip circumference and waist height ratio with screen sedentary time and non-screen based sedentary time4.Difference in the mean SST and mean NSST between the intervention and control group

### Data management

Utilizing IBM SPSS (Statistical Package for Social Sciences) Statistics for Windows Version 25.0, the gathered data will be coded, inputted, and analyzed. Armonk: IBM Corporation.
^
33
^ The proformas will be checked for completeness and the participant will be contacted for any missing information. The data will be kept confidential and protected using encryption.

### Data analysis

Proportions will be used to express the results. The interquartile range (IQR) and standard deviation (SD) associated with summary measures like mean and median will be reported for continuous variables. ITT analysis—intention to treat—will be used. The data will be represented by suitable tables and figures. The chi-square test will be used to compare variables between intervention and control groups. The baseline and post-intervention values across the intervention and control groups will be compared using the Mann-Whitney U test for non-normal data. (ST, SST, NSST) For data following normal distribution (WC, HC) independent t-test will be used and p < 0.05 will be considered to be statistically significant. Repeated measures of ANOVA will be used to compare the change scores (ST, SST, NSST) within the intervention and control groups and ’a p-value less than < 0.05 will be considered statistically significant.

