### Sample size calculation

Assuming that the proposed intervention in this study will result in a reduction in the mean screen-based sedentary time by 0.9 hours (54 minutes) between intervention and the control groups, with 80% power and at a level of significance of 5%, the sample size was calculated to be 180 in each of the intervention and control arm. A design effect of 2 was assumed since this was a cluster randomized trial, and a sample size of 360 was determined for both the intervention and control groups. The final sample size was 400 in each arm, taking into account a maximum loss of 10% throughout the six-month follow-up period.

The sample size was calculated using the following
equation ((1):

$$N=\frac{2\left[Z_{1-\frac{a}{2}}+Z_{1-\beta }\right]\sigma 2}{d^{2}}$$
(1)

Where,

*Z*
_1-
*α*/2_ = 1.96, Standard normal value at 5% level of significance

*Z*
_1-
*β*
_ = 0.84, Standard normal value at 80% power

*σ* = standard deviation = 3.025 hours
^
15
^

*d* = clinically significant difference = 0.9 hours

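### Schools are randomised, but the named between-arm tests treat pupils as independent: the true error rate is about 14–17% at the plan's own design effect, not 5%

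*Protocol article*

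**What the plan says.** **Randomisation technique.** The school is the unit: "The study will employ cluster randomization, with clusters being allocated in a 1:1 ratio to the intervention arm and control arm". The number is fixed too: "Randomization of schools will be done to accommodate 10 schools each in the intervention and control arm".

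**Sampling technique.** One class-8 section is drawn per school, "assuming a batch size of 40 students in each section".

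**Sample size calculation.** The plan recognises that pupils in one school are correlated: "A design effect of 2 was assumed since this was a cluster randomized trial". This takes 180 pupils per arm to 360, and a 10% loss allowance takes it to 400. No intraclass correlation (ICC) is given.

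**Data analysis.** Tests are named by type of variable. For screen time, SST and NSST: "The baseline and post-intervention values across the intervention and control groups will be compared using the Mann-Whitney U test for non-normal data". For waist and hip circumference: "For data following normal distribution (WC, HC) independent t-test will be used", with 0.05 as the threshold. A chi-square test compares variables between arms. Repeated-measures ANOVA is applied to change scores within each arm. None of these is described with a school effect or as run on school-level summaries.

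**The concern.** The Mann-Whitney, independent t and chi-square tests, in their ordinary form, assume that every observation is independent. Here pupils share a school, a class section and the same intervention sessions, and allocation was made to schools. With about 720 to 800 pupils entered as independent units, the tests credit the trial with far more information than 20 randomised units supply. The sample size section accepts this and pays for it by doubling the pupils; the analysis section ignores it.

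The hypothesis, and the last item under Outcome variables, is the difference in SST and NSST between arms. The named tests are the basis for that conclusion. If they reject too often, a chance imbalance between two sets of 10 schools can be reported as an intervention effect.

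**Working it through.** **Inputs from the protocol.** Difference 0.9 hours; SD 3.025 hours; z-values 1.96 and 0.84; design effect 2; 10% loss; 10 schools per arm; 40 pupils per school, so 36 after the allowed loss.

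**1. The plan's own figure.** With the sum of z-values squared:

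n = 2 × (1.96 + 0.84)² × 3.025² / 0.9² = 2 × 7.84 × 9.1506 / 0.81 = 177.1, so 178 per arm (stated 180).

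Doubled, this is 356 (stated 360), and 360 / 0.9 = 400 as stated. The equation as printed lacks the square and would give about 63, so the stated numbers come from the squared form. The design effect of 2 is therefore genuinely built into the 400.

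**2. Implied ICC.** Design effect = 1 + (m − 1) × ICC. Setting it to 2 gives ICC = 1/39 = 0.0256 at m = 40, or 1/35 = 0.0286 at m = 36.

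**3. Error rate when clustering is ignored.** The naive standard error is the correct one times 1/√2 = 0.71. The true two-sided error rate is

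2 × [1 − Φ(1.96/√2)] = 2 × [1 − Φ(1.386)] = 16.6%.

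**4. Simulation under a true null, 10 schools per arm.** The first four rows use 6,000 trials each and the last uses 4,000.

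| Setting | Design effect | Formula | Pupil-level t-test | Mann-Whitney | t-test on school means |
|---|---|---|---|---|---|
| m = 40, ICC 0.0256, normal | 2.00 | 16.6% | 16.8% | 16.4% | 5.2% |
| m = 40, ICC 0.0256, skewed | 2.00 | 16.6% | 15.0% | 15.8% | 4.6% |
| m = 36, ICC 0.0286, normal | 2.00 | 16.6% | 17.3% | 17.0% | 5.6% |
| m = 36, ICC 0.0256, normal | 1.90 | 15.5% | 15.3% | 15.0% | 4.9% |
| m = 36, ICC 0.0256, lognormal | 1.90 | 15.5% | 13.1% | 14.4% | about 5% |

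The 14% end of the range thus belongs to 36 retained pupils per school and skewed data. The 13.1% is a t-test on skewed data, which the plan does not propose: it reserves the t-test for normally distributed variables.

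**5. Other ICCs.** These are assumptions; the protocol gives none. By formula at m = 40:

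| ICC | Design effect | True error rate |
|---|---|---|
| 0.01 | 1.39 | 9.6% |
| 0.02 | 1.78 | 14.2% |
| 0.05 | 2.95 | 25.4% |
| 0.10 | 4.90 | 37.6% |

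With 36 per school and lognormal data, the simulated Mann-Whitney rates were 23.2% at 0.05 and 34.7% at 0.10.

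**The case against.** **The unit of analysis is inferred.** The Data analysis section does not say that the tests run on individual pupils. A t-test or Mann-Whitney test on 20 school means would be valid, and a fuller plan might specify it. But the article names specific tests variable by variable, sizes the trial in pupils and mentions no school means. The natural reading is pupil level, and a reader following the text would analyse it that way.

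**The range should be narrower.** At a design effect of exactly 2, 15–17% describes the results better. The 14% needs the design effect to fall to 1.90 through loss of pupils, together with skewed data. This is fair, and does not alter the conclusion.

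**The ANOVA is a separate matter.** It compares changes within each arm, so the error rates above were not derived for it. This stands. It also means that the ANOVA supplies no valid between-arm comparison.

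**Larger ICCs have no source in the document.** Correct; they are assumptions, and a smaller one lowers the rate. Even 0.01 nearly doubles the nominal level. The NSST questionnaire counts hours seated in class, which a school timetable would largely set, so strong clustering is plausible for that outcome.

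**Not every significant result would be wrong.** At a design effect of 2, a naive result with |z| above 1.96 × √2 = 2.77 (p below about 0.006) would survive correction under the normal approximation. The naive p-value alone does not show this, because the real ICC is unknown until estimated.

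**Conclusion.** The concern holds. The design and sample size respect clustering and the named between-arm tests do not; nothing elsewhere in the article repairs this. At the plan's own design effect the true two-sided error rate is 16.6% by formula and about 14–17% for the Mann-Whitney test by simulation, roughly three times nominal.

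This rests on reading the tests as pupil-level, on about 36 to 40 pupils in each of 20 schools, and on the stated design effect being right. A larger ICC makes it worse, a smaller one milder. Because the fault lies in the tests that carry the main conclusion, it must be corrected before the analysis.

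**What to change.** Replace the pupil-level between-arm tests in the Data analysis section with an analysis that respects the school as the randomised unit:

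- For SST, NSST and the other continuous outcomes, fit a linear mixed model with a random intercept for school, one for pupil where visits repeat, and Satterthwaite degrees of freedom. Report the mean difference between arms with its 95% confidence interval, and the ICC.
- As a check, or as a simpler main analysis, use a t-test (18 degrees of freedom) or a permutation test on the 20 school means. The permutation test also answers the plan's worry about non-normal data.
- For categorical outcomes, use the corresponding clustered model.
- If the within-arm ANOVA is kept, label it descriptive.

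**Cost.** One paragraph of text, no new data, and wider intervals. The pupils were already inflated for clustering, so most of the planned power remains, but 18 degrees of freedom take a little. With 36 per school and a design effect of 2, the standard error is 3.025 × √(2 × 2 / 360) = 0.319 hours. The ratio 0.9 / 0.319 = 2.82 gives 81% power by the normal approximation and 76% for the t-test on school means. With all 40 per school retained at ICC 0.0256, the latter is 80%. Current status of the study states that recruitment has not started, so the change can be made before any outcome is seen.

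### The between-arm tests of SST and NSST ignore the baseline values collected, and the rank test does not match the mean-difference outcome or the 0.9 h target

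*Protocol article*

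**What the plan says.** All places are in the Methods of the protocol article.

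- **Data analysis.** For ST, SST and NSST, "The baseline and post-intervention values across the intervention and control groups will be compared" with a Mann-Whitney U test. WC and HC get an independent t-test. No covariate is named for either. A repeated-measures ANOVA of change scores in ST, SST and NSST is also planned, but it is worded as a comparison within the two groups. Means with SD and medians with IQR are to be reported.
- **Outcome variables.** Item 4 is "Difference in the mean SST and mean NSST between the intervention and control group".
- **Sample size calculation.** The trial is sized on a "reduction in the mean screen-based sedentary time by 0.9 hours (54 minutes) between intervention and the control groups", and the same figure is called the "clinically significant difference = 0.9 hours".
- **Baseline data collection.** Questionnaires are completed at baseline and at 2, 4 and 6 months. Anthropometry is taken at baseline and month 6.
- **Randomization technique.** Ten schools per arm are allocated by simple randomization. No stratification or matching is stated.

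**The concern.** There are two linked problems, both in text that the article fixes.

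**Mismatch of test and outcome.** The outcome and the sample size concern a difference in mean hours. A Mann-Whitney test addresses rank ordering and gives neither a mean difference nor an interval in hours. The trial could report a p-value without being able to say, with stated uncertainty, how the effect compares with 0.9 h.

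**Baseline left unused between arms.** With only 20 schools allocated by simple randomization, the arms may differ noticeably in mean SST at the start. An unadjusted follow-up comparison carries part of that difference and is less precise than it need be. The repeated-measures ANOVA does use baseline, through change scores. As worded, though, it looks at change inside each group, so it gives no baseline-adjusted contrast between the arms.

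**Working it through.** **Inputs from Sample size calculation:** difference 0.9 h; "standard deviation = 3.025 hours"; two-sided 5%, 80% power; design effect 2; 360 per arm analysed and 400 recruited after 10% loss. **Assumed:** r, the correlation of a pupil's baseline and follow-up SST, taken as equal at pupil and school level. The documents give no value, so 0.2 to 0.7 is shown.

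**1. Reproduce the plan's figure.** n = 2 × (1.96 + 0.84)² × 3.025² / 0.9² = 177.1, so 178 per arm against the stated 180. Then 180 × 2 = 360, and 360 / 0.9 = 400. The plan's size reproduces. (Equation (1) as printed lacks the square on the Z bracket and would give about 64; the stated 180 matches the squared form.)

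**2. Chance imbalance at baseline.** SE = SD × √(2 × DE / n) = 3.025 × √(2 × 2 / 400) = 0.3025 h.
- 95% range: ±1.96 × 0.3025 = ±0.59 h, or 66% of 0.9 h.
- Chance of a difference above 0.30 h in either direction: about 32%.

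**3. Part carried into follow-up.** This is about r × imbalance. At the edge of the 95% range it is ±0.18 h (r = 0.3), ±0.30 h (r = 0.5) or ±0.42 h (r = 0.7).

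**4. Power with and without adjustment.** Unadjusted SE at 360 per arm = 3.025 × √(2 × 2 / 360) = 0.3189 h, so the noncentrality is 0.9 / 0.3189 = 2.82. Adjustment multiplies the SE by √(1 − r²). Power is from the noncentral t on 20 − 2 = 18 df.

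| r (assumed) | 1 − r² | SE (h) | Power |
|---|---|---|---|
| none (unadjusted) | 1.00 | 0.319 | 76% |
| 0.2 | 0.96 | 0.312 | 78% |
| 0.3 | 0.91 | 0.304 | 80% |
| 0.4 | 0.84 | 0.292 | 83% |
| 0.5 | 0.75 | 0.276 | 87% |
| 0.6 | 0.64 | 0.255 | 92% |
| 0.7 | 0.51 | 0.228 | 96% |

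On the normal approximation, the unadjusted power is 80.6%, in line with the plan's 80%. The drop to 76% comes from having only 20 schools.

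**5. Simulation check.** With 10 schools per arm, 36 pupils each, normal data, 3,000 runs, and the ICC implied by design effect 2 (1 / (36 − 1) = 0.029), an unadjusted school-level t-test had power of about 77%. School-level ANCOVA had about 78%, 85% and 95% at r = 0.3, 0.5 and 0.7. The same runs put the type I error of a pupil-level Mann-Whitney test at about 16.5%, because it ignores clustering.

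**The case against.** The strongest reply is that an unadjusted comparison is valid in a randomized trial. Chance imbalance is not bias: a correctly computed standard error already contains it, so steps 2 and 4 are largely one argument seen from two sides. That is right, and it makes adjustment a gain in efficiency rather than the repair of an invalid estimate. It does not answer the mismatch between the rank test and the mean-difference outcome.

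Four further limits stand:

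- A reader might infer that the mean difference is never estimated. The documents do not support that. It is a listed outcome, and means with SD will be reported, so a raw difference can be formed. What is absent is a stated method that gives it with a confidence interval.
- A reader might infer that baseline imbalance passes in full into the result. Only about r times the imbalance does: at r = 0.5, a 0.30 h imbalance contributes about 0.15 h.
- SST is self-reported in time bands, so r could be low. At 0.2 to 0.3, power rises by only two to four points.
- The 76% belongs to a cluster-level comparison, not to the pupil-level rank test that is planned. The table therefore shows what adjustment adds once clustering is handled, not the loss from the plan as written.

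It could also be said that an article may leave a confidence interval or a covariate list to a fuller document. That would hold if the article were silent, but it names the between-arm tests.

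**Conclusion.** The point holds in this limited form. The plan fixes unadjusted between-arm tests for measures whose baseline values it collects. For SST and NSST, the test does not match the stated outcome or the 0.9 h target, and the within-group ANOVA does not fill the gap. The mismatch needs no assumption. The gain from adjustment depends on r, which is not given: small at 0.2 to 0.3 (78% to 80%, against 76%) and material from about 0.5 (87% or more). It also assumes the plan's SD and design effect, equal correlation at both levels, and an analysis that respects clustering. For WC and HC the factor 1 − r² applies in the same way, again with r unknown. This should be changed, but it does not invalidate the randomized comparison.

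**What to change.** Replace the between-arm tests of SST and NSST, and of WC and HC, with one of two models of the follow-up value:

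- a linear mixed model with the pupil's own baseline value as covariate and school as random effect; or
- a school-level ANCOVA with the school as unit and its mean baseline value as covariate.

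Report the adjusted mean difference with its 95% CI, in hours for SST and NSST, and set the SST result against 0.9 h. If the data are skewed, use a cluster permutation test or a cluster bootstrap CI rather than a pupil-level rank test. Keep the school term: baseline adjustment alone would still leave clustering ignored. State that the repeated-measures ANOVA is a description of change within groups, or drop it.

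The cost is a change of analysis wording. No new data are needed, and the article reports that recruitment has not begun, so the change can be made before any outcome is seen.
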